## Methods and design

### Study design

The TOCOPROM study will be a double-blind, randomized, controlled, superiority, phase III trial comparing two parallel groups receiving a 48-h oral treatment by either nifedipine or placebo (1:1 ratio). The trial protocol (current version 5.0, April 2021) follows the framework of the clinical research and innovation department (Délégation à la Recherche Clinique et à l’Innovation, DRCI, Assistance Publique – Hôpitaux de Paris), which adheres to the Standard Protocol Items: Recommendations for Interventional Trials (SPIRIT) 2013 Statement for protocols of clinical trials [49].

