#### Secondary outcome measures

Prolongation of gestation will be evaluated by various different criteria:
Latency duration, defined as the interval from PPROM to delivery.Pregnancy prolongation beyond 48 h after randomization,Pregnancy prolongation beyond 1 week after randomization,Gestational age at delivery,Delivery after 37 weeks of gestation.

Maternal morbidity will be assessed by clinical diagnosis of intrauterine infection, defined as fever (maternal temperature ≥ 38 °C), with no alternative cause identified, associated with at least two of the following criteria: persistent fetal tachycardia > 160 bpm, uterine pain or painful uterine contractions or spontaneous labor, purulent amniotic fluid [21]; and endometritis, based on the association of fever (temperature ≥ 38.0 °C) with uterine tenderness, purulent or foul-smelling lochia, and in the absence of any other cause, during the first 10 days after delivery [59].

For neonatal morbidity, we will isolate each criterion included in the composite primary outcome and assess its association with the intervention. We will also study:
Severe fetal acidemia, defined as cord umbilical artery pH less than 7.00 or base deficit greater than 16 mEq/L (16 mmol/L), or both [60];Respiratory distress syndrome, defined from clinical diagnosis as the presence of clinical signs of respiratory distress (tachypnea, retractions, flaring, grunting, or cyanosis), with a requirement for supplemental oxygen with a fraction of inspired oxygen more than 0.21 and a chest radiograph showing hypoaeration and reticulogranular infiltrates;Mild or moderate BPD, defined as requiring oxygen for at least 28 days plus the need for 21% (mild) - 30% (moderate) oxygen at 56 days postnatal age or 36 weeks’ postmenstrual age or discharge, whichever comes first [53];Grades I-II IVH, defined according to Papile’s classification: subependymal hemorrhage (grade I IVH) or IVH without ventricular dilatation (grade II IVH), diagnosed by ultrasound [54];Late-onset sepsis, diagnosed from positive bacteriology findings in blood or cerebrospinal fluid (confirmed infection) that began after 72 h of life [61].

At 2 years of corrected age, we will evaluate the following criteria [51]:

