Vital status (ascertainment of whether the child died between discharge and follow-up at 2 years or is still alive);Cerebral palsy, defined according to the diagnostic criteria of the Surveillance of Cerebral Palsy in Europe (SCPE) network [62], with severity graded with the five-level Gross Motor Function Classification System (GMFCS) [63];Hearing impairment, defined as deafness or functional hearing loss requiring correction and classified as severe (bilateral) or moderate (unilateral) [64];Visual impairment, defined as blindness or the ability to see light only, and classified as severe (bilateral) or moderate (unilateral) [64]. Squinting or the need for glasses will also be recorded;Neurodevelopment, assessed with the second version of the 24-month Ages and Stages Questionnaire (ASQ), which is validated in France and covers five developmental domains: communication abilities, gross motor skills, fine motor skills, problem-solving abilities, and personal-social skills [64, 65].

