### Statistical issues

#### Sample size

Within the prospective, national, population-based EPIPAGE-2 cohort study of preterm births, we selected a sample of 888 women according to the TOCOPROM eligibility criteria and estimated the frequency of infants diagnosed with any criterion of the composite primary outcome to be 35.5%. This is an average estimate taking into account the expected variation of gestational age at birth in our study population from 22 to 37+ weeks. This estimate is consistent with findings in recent studies [15, 52, 66].

We hypothesized that the beneficial effect of tocolysis would be mediated by both higher gestational age at birth and the administration of a complete course of antenatal corticosteroids. The EPIPAGE-2 study showed that among women with PPROM, each one-day increase in gestational age at birth is significantly associated with a reduced relative risk (RR) of fetal or neonatal death or severe morbidity (RR 0.95, 95% CI 0.91–0.99) [10]. With pregnancy prolonged by 48 h by effective tocolysis, we expect to reduce the rate of fetal or neonatal death or severe morbidity by 10%. Each additional day after the initial 48-h period will also contribute to reducing adverse outcomes. Moreover, this initial prolongation will allow a complete course of antenatal corticosteroids, with additional beneficial effects, as shown by Roberts et al. [28, 67]. In meta-analyses of women with PPROM, antenatal steroids have been associated with reduced perinatal (RR 0.59, 95%CI 0.39–0.90) and neonatal mortality (RR 0.61, 0.46-0.83), respiratory distress syndrome (RR 0.70, 0.55-0.90), chronic lung disease (RR 0.50, 0.33–0.76), necrotizing enterocolitis (RR 0.39, 0.18–0.86), and IVH (RR 0.47, 0.28-0.79). Retinopathy of prematurity, early-onset sepsis, and periventricular leukomalacia were not analyzed separately by membrane status in these meta-analyses.

When we assume an alpha-risk of 0.05 and a beta-risk of 0.20 (i.e., statistical power of 80%), 702 women (351 per arm) are required to show a reduction of the primary endpoint from 35% (placebo group) to 25% (nifedipine group). We plan to increase the required number of subjects by 20%, to replace patients who leave the study early. The total number of subjects required is thus 850.

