#### Statistical analysis

Data analysis and reporting will follow the CONSORT guidelines for randomized controlled trials [68] and will be conducted according to the following principles. The trial statistician and researchers will be blinded to group status. No intermediate analysis is planned, as there is no added risk for women and neonates from this study compared with routine practices in France. Data will be analyzed by the intention-to-treat principle, i.e., all randomized participants will be analyzed according to their original allocation, regardless of protocol adherence. Baseline demographic and clinical characteristics of women, including adherence to the protocol, and outcomes will be described and compared by allocated treatment. Categorical variables will be summarized by numbers and percentages of patients in each treatment group and compared by Chi-2 or Fisher’s exact tests, as appropriate. Quantitative variables will be presented as means (standard deviations) if their distribution is normal and medians (interquartile ranges) otherwise; they will be compared with Student or Mann-Whitney-Wilcoxon tests, as appropriate. All these statistical tests will be two-sided and the level of statistical significance will be set at 5% (2-sided).

The effects of tocolysis will be expressed as relative risks with their 95% CIs for categorical outcomes and as mean differences with their 95% CIs for quantitative outcomes. Risk ratios and 95% CIs will be calculated for the primary outcome by using Poisson regression with a robust variance estimation, first unadjusted and then adjusted for minimization factors. Center will be fitted as a random effect, and the other minimization factors as fixed effects. The results will also be expressed as absolute risk differences with 95% CIs for binary outcomes. We will assess the Number Needed to Treat (NNT), defined as the number of patients who must be treated to prevent one additional adverse outcome.

Secondary outcome measures will be approached similarly to the primary outcome measure. Latency duration will be evaluated by Kaplan-Meier estimators and compared between the two treatment groups with the Log rank test and Cox proportional hazards regression, adjusted for gestational age at PPROM, if the proportional risks hypothesis is verified.

As a secondary analysis, we will analyze a per-protocol population, namely, women who received the full experimental treatment (eight tablets of nifedipine or placebo).

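### Late neonatal components and 2-year impairments are compared one at a time although death prevents or cuts them short; no 2-year criterion counts fetal and in-hospital deaths

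*Protocol article*

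**What the plan says.** All places are in the protocol article.

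- **Primary outcome measure.** Fetal death from randomization, neonatal death to discharge (at most 24 weeks after birth) and severe neonatal morbidity form one composite, so death is an event. Severe BPD needs at least 28 days of oxygen plus an assessment at 56 days, 36 weeks' postmenstrual age or discharge.
- **Secondary outcome measures, neonatal.** "we will isolate each criterion included in the composite primary outcome and assess its association with the intervention". Further neonatal conditions are added singly.
- **Secondary outcome measures, 2 years.** Cerebral palsy, hearing, vision and neurodevelopment are separate criteria. Vital status is another, described as "ascertainment of whether the child died between discharge and follow-up at 2 years or is still alive".
- **Statistical analysis.** "Secondary outcome measures will be approached similarly to the primary outcome measure", that is, by relative risks, with all randomized participants analyzed as allocated. Data judged missing at random are multiply imputed; otherwise participants with missing data are excluded. Death is not mentioned in that rule.
- **Sample size.** The benefit is expected to come partly through complete steroid courses, for which RRs of 0.59 (perinatal death) and 0.61 (neonatal death) are cited.

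**The concern.** The primary composite handles death correctly. Isolating its later parts removes that protection. An infant who dies early cannot go on to meet the definition of severe BPD, may die before retinopathy develops, and can have no impairment at 2 years.

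The stated methods leave three ways to treat such an infant: counted as free of the condition, excluded, or imputed as if missing. The first gives a valid randomized comparison of incidence, but one in which an early death looks like a good result. The second compares survivors, who are no longer a randomized group. The third assigns a dead child an outcome that does not exist.

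If nifedipine saved fragile infants, some would develop BPD and the single RR could look like harm. If it raised mortality, real harm could be hidden. This matters because the abstract names neonatal death and long-term sequelae as the risk of prolonging exposure, and the late components and 2-year results bear on that risk directly.

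**Working it through.** **The plan's own figure.** 35% v 25%, two-sided 5%, 80% power, 1:1. Without continuity correction, n = [1.96√(2×0.30×0.70) + 0.8416√(0.35×0.65 + 0.25×0.75)]² / 0.10² = 328.5, so 329 per arm. With continuity correction, (328.5/4) × [1 + √(1 + 4/(328.5×0.10))]² = 348.2, so 349 per arm. The stated 351 per arm is reproduced within 1%. It concerns the primary composite, which already includes death, so nothing below changes it.

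**Model.** The article gives no death or component rates by arm, so the rates below are assumptions.

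- d0, d1: death risk on placebo and nifedipine. Infants saved: d0 − d1.
- q: component risk in infants who survive under either arm, equal in both arms (no effect on morbidity).
- s: component risk in saved infants.
- Dying infants are first taken never to meet the definition.

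Component risk is C0 = (1 − d0)q on placebo and C1 = C0 + (d0 − d1)s on nifedipine.

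**Illustration.** d0 = 10%, d1 = 7%, q = 8%, s = 50%.

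- C0 = 0.90×0.08 = 0.072; C1 = 0.072 + 0.03×0.50 = 0.087.
- All randomized: 0.087/0.072 = **1.21**.
- Survivors: (0.087/0.93)/(0.072/0.90) = **1.17**.
- Death or BPD: (0.07 + 0.087)/(0.10 + 0.072) = **0.91**.

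With death 12% v 8%, C0 = 0.0704 and C1 = 0.0904, so the three RRs are 1.28, 1.23 and 0.1704/0.1904 = 0.89.

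**Reverse direction.** Swapping the arms (nifedipine raises death from 7% to 10%) gives a BPD RR of 0.072/0.087 = 0.83 in all randomized, against death-or-BPD of 0.172/0.157 = 1.10. The harm is then hidden.

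**Range.** q = 10%, s = 30–50%, no effect on morbidity. A death RR of 0.59 is the article's steroid figure; 0.75 is a milder assumption.

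| Placebo death | Death RR | Component RR, all randomized | Component RR, survivors | Death-or-component RR |
|---|---|---|---|---|
| 5% | 0.59 | 1.06–1.11 | 1.04–1.08 | 0.90–0.93 |
| 10% | 0.59 | 1.14–1.23 | 1.09–1.17 | 0.85–0.89 |
| 10% | 0.75 | 1.08–1.14 | 1.05–1.11 | 0.91–0.93 |
| 20% | 0.59 | 1.31–1.51 | 1.19–1.37 | 0.80–0.85 |

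**What shrinks or masks it.**

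- *Saved infants at average risk* (s = q = 10%, death RR 0.59, placebo death 5–20%): the survivor RR is 1.00 and the all-randomized RR 1.02–1.10.
- *Some dying infants meet the definition first.* If a share f of deaths does, the first illustration gives (0.087 + 0.07f)/(0.072 + 0.10f). This falls from 1.21 at f = 0 to 0.122/0.122 = 1.00 at f = 0.5. Death-or-BPD stays 0.91, because those infants are already events.
- *Morbidity falls too.* Apply 25/35 = 0.71, or the article's steroid RR of 0.50 for chronic lung disease, to infants who survive either way. With death 10% v 7%, BPD RR = (0.072×0.71 + 0.015)/0.072 = 0.92, or (0.036 + 0.015)/0.072 = 0.71. With 12% v 8% it is 0.99 or 0.78.
- *Break-even.* At 10% placebo death, death RR 0.59, q = 10% and s = 30–50%, the observed RR stays below 1 only if the true RR in infants surviving either way is below about 0.77–0.86 (all randomized) or 0.82–0.91 (survivors).

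**Precision.** With 850/2 = 425 per arm, the first illustration gives about 31 v 37 BPD events. SE(log RR) = √(1/37.0 + 1/30.6 − 2/425) = 0.235, so RR 1.21 has a 95% CI of about 0.76–1.91.

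**The case against.** **The analysis plan may settle it.** The Ethics section says that a statistical plan was written before the trial started. How deaths enter each denominator could well be fixed there, and its absence from a condensed article is no finding. That stands. But the article itself fixes the single-outcome comparisons, a vital status that begins at discharge and a missing-data rule that does not separate death from missingness. The plan would have to add to these or depart from them.

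**Not only survivors can have these conditions.** A reader might infer that BPD, retinopathy, late-onset sepsis and leukomalacia are observable only in infants who live. The definitions do not support that: an infant can meet them and die later in the stay. Death truncates these outcomes; only the 2-year impairments strictly require survival.

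**Deaths are visible.** Fetal and neonatal death are themselves isolated components, so mortality will stand beside morbidity. That stands and limits the damage, although seeing both does not combine them. A reader might also infer that earlier deaths are lost from the trial. They are not: they are recorded for the primary outcome. The gap is that no 2-year criterion counts them.

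**The illustration is chosen.** It assumes no morbidity benefit, whereas the design assumes one, and with that benefit the apparent harm disappears. This stands, and even the adverse case would be inconclusive at this sample size. So the documents do not support a prediction that tocolysis will look harmful, only that the single RRs can mislead.

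**Composites can hide signals.** Replacing single-component tests by death-or-condition could let fewer deaths mask more infection. This stands, so the single analyses should be kept.

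**Conclusion.** The point holds as a limit on interpreting secondary results. For severe BPD, retinopathy and every 2-year impairment, the single-outcome RR can mislead in either direction if mortality differs between arms, and the article's rationale expects that it will. With no effect on morbidity, the assumed rates give component RRs of about 1.1 to 1.5 in all randomized and 1.0 to 1.4 in survivors, while death-or-component lies at about 0.8 to 0.9.

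These sizes rest on death and component rates that the article does not give, and on saved infants being sicker than average. The death RR of 0.59 belongs to steroids, not to tocolysis. The firmest part needs no assumed rate: as written, no 2-year criterion includes fetal and in-hospital deaths. The primary analysis and its sample size are not affected.

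**What to change.** 1. Keep the single-component analyses, and read each RR beside the mortality results.
2. Add death since randomization or the condition, in all randomized, for severe BPD and for retinopathy.
3. Make death since randomization or moderate/severe impairment at 2 years the main 2-year comparison in all randomized, with the impairment thresholds set in advance in the analysis plan.
4. Define 2-year vital status from randomization, so that it includes fetal and in-hospital deaths.
5. State that outcomes of dead infants are not missing data and are not multiply imputed.

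The cost is wording in the protocol and analysis plan, fixed before unblinding. Deaths and conditions are already due to be collected. The drawbacks are that composites are less specific for each condition, and that 2-year data still depend on the second parental consent and on return of the questionnaire.

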### Data collection, management, and monitoring

Maternal adverse events will be recorded prospectively from the first nifedipine or placebo intake to the end of follow-up. Maternal and obstetric data will be available in medical files and will be recorded on the electronic case report form (e-CRF) after the end of the follow-up period. Although this situation is unlikely, if a patient delivers outside the recruiting maternity unit, a duplicate of the medical record will be requested to collect all necessary data.

Neonatal deaths will be reported prospectively. All neonatal data will be recorded on the e-CRF based on medical files, after the infant’s discharge. In NICUs, hospital reports are very precise and state clearly all pathologies and complications diagnosed during the stay. Diagnoses generally use international definitions and are therefore standardized. If any neonate is transferred to a NICU outside of the recruiting center, the investigators will request the hospital report and/or a duplicate of the medical file to collect all necessary data.

This study, including quality controls, will be conducted according to the standard operating procedures of the sponsor, Assistance Publique – Hôpitaux de Paris (AP-HP), the Declaration of Helsinki, and Good Clinical Practices. All data will be recorded by local investigators, research midwives, or trained clinical research technicians on a secure eCRF. Local investigators will be responsible for the accuracy, quality, and relevance of all the data entered. Specific codes will be entered for data missing in the medical records, to distinguish them from data entry errors. Cross-checks for completeness and consistency checks will take place periodically.

Data management will be handled centrally by the Clinical Research Unit (Paris Descartes Necker Cochin) with the study’s Scientific Directors ([name]). A data management plan will be written and followed throughout the entire data management and analysis process. Clinical research assistants will organize periodic contacts and monitoring visits to each recruiting center. These will include a telephone contact within 2 weeks of the first inclusion, an onsite visit within 3 months of the first inclusion, and then a visit every 10 inclusions or once a year, whichever comes first. Compliance with the research protocol and procedures, consent forms, and predefined relevant data (eligibility criteria, adherence, primary and secondary outcome measures, and severe adverse events with immediate notification) will be monitored onsite, while severe adverse events without immediate notification and 2-year outcomes will be monitored remotely. All study documents will be archived by the investigators and the sponsor for 15 years after the end of the trial.

### Confidentiality and data handling

Data will be handled according to the French (amended “Informatique et Libertés” law governing data protection) and European (General Data Protection Regulation, GDPR) regulations. The eCRFs will be hosted by a service provider in a secure electronic system via a web navigator and protected by an individual password for each investigator and clinical research technician.

The full identity of the research participants and their contact details will be recorded for purposes of the 2-year follow-up, with the authorization of the French Data Protection Agency (CNIL, Reference 919221, August 2, 2019). Identity and contact details will be kept separately from clinical data. To ensure confidentiality, participant’s identifying information will be replaced by an identification code specific to the study indicating the order of enrolment.

The steering committee will have access to the full anonymized trial dataset. The trial database file will be stored for 15 years. The sponsor is the owner of the data.

### Statistical issues

#### Sample size

Within the prospective, national, population-based EPIPAGE-2 cohort study of preterm births, we selected a sample of 888 women according to the TOCOPROM eligibility criteria and estimated the frequency of infants diagnosed with any criterion of the composite primary outcome to be 35.5%. This is an average estimate taking into account the expected variation of gestational age at birth in our study population from 22 to 37+ weeks. This estimate is consistent with findings in recent studies [15, 52, 66].

We hypothesized that the beneficial effect of tocolysis would be mediated by both higher gestational age at birth and the administration of a complete course of antenatal corticosteroids. The EPIPAGE-2 study showed that among women with PPROM, each one-day increase in gestational age at birth is significantly associated with a reduced relative risk (RR) of fetal or neonatal death or severe morbidity (RR 0.95, 95% CI 0.91–0.99) [10]. With pregnancy prolonged by 48 h by effective tocolysis, we expect to reduce the rate of fetal or neonatal death or severe morbidity by 10%. Each additional day after the initial 48-h period will also contribute to reducing adverse outcomes. Moreover, this initial prolongation will allow a complete course of antenatal corticosteroids, with additional beneficial effects, as shown by Roberts et al. [28, 67]. In meta-analyses of women with PPROM, antenatal steroids have been associated with reduced perinatal (RR 0.59, 95%CI 0.39–0.90) and neonatal mortality (RR 0.61, 0.46-0.83), respiratory distress syndrome (RR 0.70, 0.55-0.90), chronic lung disease (RR 0.50, 0.33–0.76), necrotizing enterocolitis (RR 0.39, 0.18–0.86), and IVH (RR 0.47, 0.28-0.79). Retinopathy of prematurity, early-onset sepsis, and periventricular leukomalacia were not analyzed separately by membrane status in these meta-analyses.

When we assume an alpha-risk of 0.05 and a beta-risk of 0.20 (i.e., statistical power of 80%), 702 women (351 per arm) are required to show a reduction of the primary endpoint from 35% (placebo group) to 25% (nifedipine group). We plan to increase the required number of subjects by 20%, to replace patients who leave the study early. The total number of subjects required is thus 850.

